### Data collection and management

General baseline information will be collected about patients when they are sent to the hospital.

Primary outcomes will be assessed using the FSS on every weekend, and the secondary outcomes will be performed at the end of the 4th week of treatment. Complications during follow-up will also be assessed. If the patient is still in the hospital, the investigator may visit the patient on the ward to go through the evaluation. If the patient has been discharged, his or her legal representative will be told to come back in due time for assessment after leaving the hospital. If the patient does not arrive, the investigator will try to contact the patient or the family members by telephone. Other possible methods may also be used to explain the situation and complete the outcome assessment. If all attempts fail, no further contact will be made, and the patient will be recorded as lost to follow-up.

All the data will be collected by independent investigators who are blind to the patient’s allocation. Each local study center will assign a specific investigator at the beginning of the trial. This investigator will be excluded throughout the treatment of all the participants unless asked by clinicians to perform the assessment.

All variables specified in the protocol will be documented on standardized hard-copy case report forms (CRFs) in all participating centers. When the 8-week follow-up is complete, data in the CRF of each patient will be validated for completeness, consistency, and plausibility, by an independent investigating physician in a local center. Then the CRF will be transmitted to the Center of Evidence Based Medicine, NCU, which will be responsible for the development of a central database, and data entry and storage. At the end of the trial, the database will be locked and sent to the study statistician for analysis based on a predetermined statistical analysis plan.

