### Trial outcomes

#### Outcome measures

In this study, primary outcomes will be measured at baseline and at the end of every week from the 1st to the 4th week. Secondary outcomes will be measured at baseline and the end of the 4th week. During each treatment, adverse events and untoward effects will be assessed. All outcome assessments will be independently performed by experienced and blinded assessors, the same one professional rehabilitation physician. A summary of all the measures in the trial is shown in Table 1.

**Table 1 Tab1:** Data on the design of the study

Point in time	Screening stage	Treatment period 1 (1 week)	Treatment period 2 (2 weeks)	Treatment period 3 (3 weeks)	Treatment period 4 (4 weeks)
Informed consent	**×**				
Inclusion and exclusion criteria	**×**				
Withdrawal, drop out, and termination criteria		**×**	**×**	**×**	**×**
Basic information	**×**				
Past medical history	**×**				
Therapeutic parameter record		**×**	**×**	**×**	**×**
**(*****Baseline*****) Fatigue Severity Scale (FSS)**	**×**	**×**	**×**	**×**	**×**
**Functional Assessment Chronic Illness Therapy (Fatigue) (FACIT-F)**	**×**				**×**
**Fatigue Impact Scale (FIS)**	**×**				**×**
**Specialized Quality of Life Scale in Stroke (SS-QOL)**	**×**				**×**
Overall efficacy evaluation					**×**
Complications	**×**	**×**	**×**	**×**	**×**
**Adverse events recorded**	**×**	**×**	**×**	**×**	**×**

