### Follow-up

After the 4-week treatment period, the patients will be followed up for 8 weeks. The medical staff will follow up with the participants by phone. Participants will be contacted every 2 weeks to record medication and rehabilitation. During the last week of follow-up (the 8th week after the intervention), participants will be referred for clinical evaluation to assess their prognosis and disability status.

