### Statistical methods

#### Statistical analysis

Statistical methods using statistical analysis software SPSS21.0 will be used to analyze the test results. In the descriptive analysis of samples, the continuous variables are expressed in mean and standard deviation for the data of normal distribution and in the range of median and quartile for the data of non-normal distribution. The normally distributed packets are compared statistically between the *t* test groups. The ordinal level variables of the non-normal distribution are compared statistically with the Mann-Whitney *u* test. Measures with discrete distributions will be expressed as percentages and analyzed using accurate tests of either chi-square *Χ*^2^ or Fisher, as appropriate. If necessary, we will use the general linear model or logit model to adjust for confounding effects.

We will use the *t* test or the Mann-Whitney test to compare baseline characteristics between the different groups. If there is statistical significance, inequality will be treated as a confounding factor in the final efficacy analysis. In order to compare one-time or two-time results between groups, the continuous data will be analyzed by *t* test or non-parametric test, and the data will be analyzed by Pearson chi-squared or Fisher precision test. In order to control the possible confounding variables, linear models or linear regression models will be used for dependent continuous variables and dependent classified variables. The subgroup analysis of the main results will be stratified according to the sex of the participants. Analysis of variance will be used to repeat the measurement data. The analysis of primary and secondary outcomes will be based on intention-to-treat (ITT) and a per-protocol (PP) basis. The results of the ITT analysis will be compared with those of the PP analysis to determine if they are consistent. The missing data will be treated as the last carrier of observation. Adverse events will be listed and analyzed using either a chi-square test or Fisher’s precision test.

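### After one assessment at which every contact route fails, the protocol ends contact for good and provides for no new attempt at later assessments, week 4 included

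*Protocol article*

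**What the plan says.** The schedule is in the protocol article under Outcome measures: "primary outcomes will be measured at baseline and at the end of every week from the 1st to the 4th week". The three secondary scales (FIS, FACIT-F and SS-QOL) are taken only at baseline and at the end of week 4. Under Follow-up, an 8-week period after treatment has telephone calls ("Participants will be contacted every 2 weeks to record medication and rehabilitation") and a clinic evaluation in its last week.

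Data collection and management has one paragraph on obtaining these assessments. It opens with the weekly FSS, the week-4 secondary outcomes and complications during follow-up, and then sets out a sequence:

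- In-patients: "If the patient is still in the hospital, the investigator may visit the patient on the ward to go through the evaluation".
- Discharged patients are asked, through their representative, to return.
- On non-arrival: "If the patient does not arrive, the investigator will try to contact the patient or the family members by telephone".
- Then: "Other possible methods may also be used to explain the situation and complete the outcome assessment".
- Finally: "If all attempts fail, no further contact will be made, and the patient will be recorded as lost to follow-up".

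The Statistical analysis section promises intention-to-treat and per-protocol analyses. On gaps in the data it says: "The missing data will be treated as the last carrier of observation". I read this as last observation carried forward (LOCF).

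**The concern.** The last step of the sequence gives the patient a permanent status, yet what triggers it is failure at a single assessment. The paragraph covers every assessment from week 1 onwards, so the rule can take effect well before the time point that matters most. A gap that might have been temporary then becomes permanent because the plan stops trying.

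Two features of the plan make this costly. First, LOCF would put a week-1 or week-2 FSS, or the baseline value, in place of the week-4 value. Second, the secondary scales have no value between baseline and week 4, so LOCF would give exactly zero change on all three. The intention-to-treat analysis most needs outcomes from patients who have stopped attending, and an outcome never sought cannot be recovered in the analysis. Complications during follow-up would also go unrecorded for these patients.

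**Working it through.** The plan gives no figure for this point. It states no chance of failed contact, no share of patients discharged before week 4, and no number of attempts or period over which they are made. The check is therefore a reading of the text, followed by an illustration on stated assumptions.

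**Reading**

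1. *Trigger.* Non-arrival alone does not trigger the rule. The telephone call to patient or family and the other methods must all fail, and those methods may themselves complete the assessment.
2. *Consequence.* No further contact, and a status recorded for the patient rather than for the visit.
3. *Scope.* The paragraph names the weekly FSS, the week-4 scales and follow-up complications, and gives one procedure for all of them. Nothing confines the last step to the final assessment or provides for another attempt at the next one.
4. *Who is exposed before week 4.* Trial design says that participants are in hospital at entry, and Interventions schedules six sessions a week over the four weeks. In-patients can be assessed on the ward. Exposure is therefore limited to patients discharged early or no longer attending.
5. *Follow-up section.* It sets two-weekly calls for participants in general and does not say whether they apply to someone already recorded as lost.

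**Illustration**

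Let q be the chance, at one visit, that the patient does not come and every route fails. This is an assumption, shown for 2% and 5%. Assume independence between visits and a patient exposed at all four.

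- Contact ends at the first failure: week-4 FSS missing with probability 1 − (1 − q)^4.
- Contact tried again at each visit: week-4 FSS missing with probability q.

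For q = 2%: 1 − 0.98^4 = 1 − 0.92237 = 0.0776, or 7.8%, against 2%.
For q = 5%: 1 − 0.95^4 = 1 − 0.81451 = 0.18549, or 18.5%, against 5%.

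Over all randomized patients, these must be multiplied by the share s who are exposed, which is unknown:

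| Assumed s | q = 2%: contact ended / tried again | q = 5%: contact ended / tried again |
|---|---|---|
| 20% | 1.6% / 0.4% | 3.7% / 1.0% |
| 50% | 3.9% / 1.0% | 9.3% / 2.5% |
| 100% | 7.8% / 2.0% | 18.5% / 5.0% |

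Two things make the difference smaller still. A patient exposed only at weeks 3 and 4 has 1 − (1 − q)^2 in place of the fourth-power term: 1 − 0.98^2 = 3.96% or 1 − 0.95^2 = 9.75%. And if the same patients stay unreachable from visit to visit, both rules give a loss of q and the gain from trying again is nil.

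**The case against.** The strongest case against is that the rule takes effect only after a reasonable search. During treatment nearly every patient is on site six days a week. To trigger the rule before week 4, a patient must have left hospital or stopped attending, and be unreachable directly, through family and by any other means. Such a patient may well be unreachable the following week too. The article also does not say over what period attempts are made, so all attempts could be taken to span later scheduled dates. A condensed article may leave such detail to the full protocol.

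Most of this stands as a limit on size. It does not remove the point, because the article is not silent: it states a rule that ends contact and attaches a permanent status. The per-assessment reading is the literal one, although the text does not spell it out.

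Four stronger readings are tempting and are not supported:

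- *That a single missed weekly visit is enough.* It is not. A patient reached by any route stays in follow-up.
- *That about 19 rather than 5 of 100 patients would be lost, close to the whole 20% dropout allowance.* This is the bottom right cell of the table. It needs every patient to be exposed at all four visits, q = 5%, and independence.
- *That the rule flatly contradicts the two-weekly calls.* Those are a general schedule, and the rule can be read as an exception to it. The two need reconciling.
- *That those lost are willing but more fatigued, or felt no benefit.* This is plausible, but nothing in the documents shows it. What can be said is that the rule does not depend on withdrawal of consent.

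**Conclusion.** The point holds as a defect in a stated conduct rule. As written, one assessment at which all routes fail ends contact permanently, whichever assessment it is. A patient affected at weeks 1 to 3 loses every later FSS, all three secondary outcomes and the post-treatment contacts, and LOCF fills the gap with an early or baseline value.

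The size cannot be derived from the documents. The range of 7.8% to 18.5% against 2% to 5% applies only to patients exposed at all four visits, rests on an assumed q of 2% to 5%, and is an upper bound because independence is the case most favourable to trying again. For the whole trial it shrinks in proportion to the exposed share, which may be small. The change is worth making because it is cheap and protects the week-4 outcomes, not because a large loss has been shown.

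**What to change.** Replace the sentence in Data collection and management with wording such as:

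*If all attempts fail, that assessment is recorded as missed, with the reason. Contact is attempted again at each later scheduled assessment, week 4 above all, and at the evaluation 8 weeks after treatment, unless the participant has withdrawn consent to contact. Lost to follow-up is assigned only after the final scheduled contact has failed.*

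Add a clause under Follow-up stating that the two-weekly calls are also attempted for participants with earlier missed assessments, so that the two sections agree.

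The cost is the change of wording and a few extra calls by existing staff. The one statistical downside is more intermittent missing-data patterns to describe. No treatment or clinical rule changes.

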### Data Safety and Monitoring Committee (DSMC)

The project will be monitored by the DSMC, initiated by the clinical trial center of The First Affiliated Hospital of Nanchang University, and composed of specialists in rehabilitation, ethics, statistics, and methodology. It is independent from the sponsor and has no competing interests. The Project Management Group and DSMC will audit the study through regular interviews or telephone calls once a week. Based on its review the DMC provides the sponsor with recommendations regarding study modification, continuation, or termination.

### Ethics approval and consent to participate

The research study “Effects of transcranial direct current stimulation on patients with post-stroke fatigue” has been approved by the Ethics Committee of the First Affiliated Hospital of Nanchang University: Clinical Medicine Ethics Review [2015]043 in Nov 2015. All family members of study participants will be informed of the trial details and their consent obtained by the doctors from the intensive-care unit and rehabilitation medicine department of First Affiliated Hospital. Before the trial, doctors will conduct a session to inform the participants and their families about the principles, precautions, and adverse reactions of the trial. On the consent form, participants will be asked if they agree to the use of their data should they choose to withdraw from the trial. Participants will also be asked for permission for the research team to share relevant data with people from the universities taking part in the research or from regulatory authorities, where relevant. This trial does not involve collecting biological specimens for storage. All of the relevant files are available from the corresponding author on request.

### Dissemination

The results will be published in a peer-reviewed journal 6 months after the trial ends. But no personal information about any of the participants will be disclosed.

### Patient and public involvement

This research will be carried out without any patient involvement. The patients will neither be involved in the design of the trial nor consulted to obtain or interpret the results. Patients will not be invited to contribute to the writing or editing of this document for readability or accuracy. Before publication, the results of this study will not be disseminated to patients or the public.

### Trial status

This protocol version number is V1.1. We plan to start recruiting patients for the trial on 1 December 2020, and it is expected to end on 30 June 2022. The experiment is expected to be completed by 2025.

### Data sharing

We will publish the experimental plan and research results as an article within 6 months after the trial ends and provide relevant materials for researchers who need a trial dataset. It will be published on the website of the First Affiliated Hospital of Nanchang University. There will also be a link attached if we publish our trial result in a peer-reviewed journal. The full protocol, participant-level dataset, and statistical code will be available upon email request, provided it is used only for scientific research.

## Discussion

As a new method of brain function research and treatment, tDCS has the advantage of being a painless, noninvasive, simple operation with a curative effect. As a non-invasive brain stimulation technology, tDCS can stimulate or inhibit the cerebral cortex and promote plasticity and functional reorganization of the functional areas of the cerebral cortex to encourage rehabilitation in stroke [34, 35]. Some studies show that it can help with fatigue [36]. In terms of fatigue symptoms, the stimulation sites of tDCS in clinical research include the bilateral M1 area, bilateral S1 area, and left DLPFC. Ferrucci et al. studied 23 MS patients with bilateral M1 area anode electrical stimulation, Tecchio et al. treated 10 MS patients with S1 area electrical stimulation, and the patients’ fatigue was reduced [37]. Chalah et al. compared the effects of the left DLPFC and right posterior parietal cortex (PPC) on MS fatigue. The results showed that left DLPFC improved fatigue symptoms, while right PPC reduced emotional scores. In order to ensure the authenticity of the test results, a double-blind test design will be adopted. Fatigue Severity Scale (FSS), Fatigue Impact Scale (FIS), Functional Assessment Chronic Illness Therapy (Fatigue) (FACIT-F), and Specialized Quality of Life Scale in Stroke (SS-QOL) will be used as evaluation indices to evaluate the changes of patients’ fatigue. The aim of this project is to investigate the effect of tDCS on post-stroke fatigue and find new interventions to improve PSF.

The related scale used to evaluate the fatigue degree of patients is greatly affected by the subjective factors of patients. Therefore, the experimental results are easily affected by various factors, such as the favorite degree of therapists. However, the FSS has good internal consistency, reliability, construct, and criterion validity and is sensitive to change. It has been evaluated in several conditions where it is the recommended fatigue scale [38, 39]. Thus, we can maximize the accuracy of the experiment.

In addition, because this experiment is based on a small sample, it forms an integral aspect of our future research work to provide a new medical basis for the treatment of patients with tDCS. Because of the high incidence of post-stroke fatigue, which has a great impact on the life of patients, it is particularly important to explore an effective way to treat post-stroke fatigue. This experiment on the therapeutic effect of tDCS on PSF will provide a new direction. This experiment is an active exploration for the treatment of PSF.

## Abbreviations

tDCS: Transcranial direct current stimulation
PSF: Post-stroke fatigue
DLPFC: Dorsolateral prefrontal cortex
FSS: Fatigue Severity Scale
FIS: Fatigue Impact Scale
FACIT-F: Functional Assessment Chronic Illness Therapy (Fatigue)
SS-QOL: Specialized Quality of Life Scale in Stroke
NCU: Nanchang University
FES: Functional Electrical Stimulate
MS: Multiple sclerosis
RA: Rheumatoid arthritis
PsA: Psoriatic arthritis
PSS: Primary Sjögren’s syndrome
OA: Osteoarthritis
SLE: Systemic lupus erythematosus
ITT: Intention-to-treat
PP: Per-protocol
AEs: Adverse events
PPC: Posterior parietal cortex
